#### Feasibility

Feasibility will be determined by successful completion of the three-week treatment course.

### Estimated duration of individual subject participation

Anakinra treatment commences at 3-24 hours of postnatal life and ceases on postnatal day 21. Treatment will continue until day 21 unless one of the following occurs: a suspected unexpected serious adverse reaction; acute kidney injury (which would increase dose-normalised exposure in the unlikely setting of immature non-renal clearance); neutropenia; or elevation of liver enzymes (details below). To monitor for these events and as part of standard care, the following blood tests will be sent to the routine pathology laboratory on days 1, 3, 7, 14, and 22 after starting IL-1Ra infusions in addition to plasmatic and cellular immunity analysis: full blood count, liver enzyme tests, urea, electrolytes and creatinine.

Treatment will cease if consent is withdrawn, in which case consent will be sought for the infant to remain enrolled and data collection to continue to enable intention-to-treat analysis. Rates of withdrawal of consent will be monitored to detect differential dropout, which can bias clinical trial results and reduce the power of the trial to detect important differences. Treatment will also cease if death is imminent and the treating team with the parents have made the decision to redirect care.

Collection of data will continue until 2 years of age, with a review at 3 months corrected age (i.e. 3 months after the infant reaches an age that equates to 40^0^ weeks GA) in the Early Neurodevelopmental Clinic (including a Prechtl’s general movements assessment), and a neurodevelopmental review at 2 years.

### Anakinra product information

Anakinra is a recombinant, non-glycosylated formulation of human IL-1Ra. It is nearly identical to the endogenous protein, the only difference being the addition of a single methionine residue at its N-terminus. The mechanism of action is through competitively inhibiting IL-1 binding to its receptor, thus preventing activation of the pro-inflammatory cascades triggered by IL-1. Anakinra has been shown to cross the blood-brain barrier in humans and preclinical models (27).

Anakinra is registered for use in various autoimmune and autoinflammatory conditions. These include rheumatoid arthritis, Still’s disease, familial Mediterranean fever, deficiency of IL-1Ra (DIRA) and cryopyrin-associated periodic syndromes (CAPS), including neonatal-onset multisystem inflammatory disease (NOMID). Typical initial dosing in adults is 100 mg daily and in children and adolescents is 1-2 mg/kg daily. Dose can be titrated to 3-4 mg/kg daily if required in 0.5-1 mg/kg increments; and in NOMID, the dose can be incremented to a maximum of 8 mg/kg daily. Population PK analysis in children and adolescents has suggested that in a child of <10 kg weight, 3 mg/kg of anakinra administered subcutaneously (SC) daily is required to achieve equivalent exposure to 1 mg/kg SC daily in an adolescent or adult (28), consistent with allometric scaling of drug clearance (29).

Anakinra undergoes extensive renal clearance, and in the setting of severe renal impairment (glomerular filtration rate, GFR <30 ml/min/1.73 m^2^), recommendation is for the same dose size to be administered alternate daily rather than daily.

Anakinra is supplied by Swedish Orphan BioVitrium and is sourced through hospital pharmacy. Anakinra is sold in ready-made syringes containing a solution (pH 6.5) comprising disodium-EDTA (0.12 mg), NaCl (5.48 mg), sodium-citrate (1.29 mg) and polysorbate 80 (0.70 mg) in water for injection. Anakinra will be provided to the ward in tuberculin syringes containing 15 mg (0.1 ml) pre-prepared by hospital pharmacy at a dilution that renders injection of the small doses required for this trial possible.

### Clinical pharmacology

Anakinra is a relatively small therapeutic protein of 153 amino acids and a molecular weight of 17.3 kDa. It is typically administered daily by SC-injection; however, it has also been administered intravenously (IV) for a range of indications. Its initial distribution volume is equivalent to plasma, with steady-state distribution volume between plasma volume and extracellular fluid volume, reflecting some extravascular movement (30).

Therapeutic proteins are eliminated almost exclusively by proteolysis, with the amino acids and peptides produced able to be reutilised in endogenous processes (31). Proteolysis of therapeutic proteins can occur via fluid-phase hydrolysis, lysosomal degradation after receptor-mediated cellular uptake or target-mediated uptake and degradation (32). In addition, therapeutic proteins with a molecular weight of less than 60 kDa, like anakinra, are freely filtered at the kidney glomerulus, with subsequent catabolism by the proximal tubular cells, either at the intraluminal brush border or after endocytosis (31).

With a molecular weight of 17.3 kDa, anakinra is efficiently filtered at the glomerulus, with renal clearance accounting for approximately 75% of total drug elimination. When dosed IV, anakinra is rapidly cleared from plasma, requiring dosing more frequently than once daily to maintain circulating anakinra concentrations throughout the dosing interval (33). However, SC-dosing of anakinra allows for less frequent dosing, due to slow absorption from the subcutaneous depot to the systemic circulation. Subcutaneous absorption is then rate-limiting to elimination, extending the duration of exposure of anakinra.

The non-renal clearance pathway for anakinra has not been described, but anakinra can be presumed to undergo endogenous proteolysis like other therapeutic proteins (32). Extra-renal clearance is lower, however, with total clearance reduction with progressive renal impairment. In a study of adults with differing levels of renal impairment, clearance of anakinra reduced with progressive renal impairment, with a reduction of 16.5%, 50.3%, 69.7% and 74.9% for GFR bands of 50-80, 30-50, <30 ml/min/1.73 m^2^ and end-stage, respectively (30). In the setting of advanced kidney disease (estimated GFR<30 ml/min/1.73 m^2^), the recommendation is to change from daily to alternate daily dosing.

### Dose selection

There are a few reports of anakinra use in early infancy (34, 35), and no reported use from birth or in extremely premature neonates. Indeed, drug development in premature neonates more broadly remains a “blind spot” in pharmacology (36). We considered dose selection a crucial element of this trial, both for safety reasons but also to ensure prospect of direct benefit to participants. Broadly accepted ethical standards for clinical research in children require potential for direct benefit if participation leads to more than minimal risk (37), and thus Phase 1 dose-finding and pharmacokinetic ‘ADME’ (absorption, distribution, metabolism and elimination) studies are not considered appropriate. Moreover, whilst in the range of auto-immune and auto-inflammatory conditions, for which anakinra is indicated, dose is titrated to clinical response, no such clinical measure for titration exists for the indication of early-life inflammation in premature infants.

Dose selection was by simulation of exposure with various dosing regimens using predicted anakinra pharmacokinetics in extremely premature neonates, in accord with standard practice in paediatric drug development. Population PK models are mathematical-statistical models providing a quantitative description of a drug’s disposition and population variability. To extrapolate to infants and neonates, PK parameters require scaling for size, and depending on the drug elimination pathways involved, a maturation function for organ immaturity. Furthermore, simulation of concentration time course and exposure with various dosing rates and schedules is performed, to determine a dose rate and schedule that matches exposure and the concentration time course that is known to be safe and effective in older children and adults. Predictions can subsequently be confirmed by comparing predictions with observed exposure, i.e. measured drug concentrations.

Data were sourced from the published literature as well as regulatory submissions, with relevant examples of observed exposure presented in **Table 1**. and pharmacokinetic parameters in **Table 2**.

**Table 1 T1:** Example anakinra dose and exposure values from published literature.

Reference	Population	N	Dose	Route	AUC_0-24h_ (mg/lxh)	Cmax (mg/l)
Yang B et al. (30)	PD HDx Normal GFR	10 10 12	1 mg/kg	IV	63.7^a^ ( ± 9.6) 64.2 ^a^ ( ± 14.9) 9.6 ( ± 1.4)	15.6 ( ± 6.5) 14.5 ( ± 3.3) 22.4 ( ± 4.9)
Yang B 2003 (30)	GFR<30	12	100 mg	SC	39.4 ( ± 4.3)	2.2 ( ± 0.7)
Yang B et al. (38)	Adults	7	100 mg	IV	14.7 ( ± 3.4)	32.2 ( ± 6.4)
Galea et al. (27)	Adults, SAH	29	100-500 mg	IV		34-102.8 (predicted)
Urien et al. (28)	Children	87	2-10 mg/kg	SC	9.6	
Study 03-AR-0298 (39)	CAPS	21 (17 Paed)	Initial: 1 mg/kg Month 3: 1.5 mg/kg Year 3: 3 mg/kg	SC	4.4 [1.8-6.9] 7.3 40.8	

a AUC_0-48h_,Target exposure based on pharmacokinetic/pharmacodynamic analysis. Concentration data expressed as mean (± standard deviation, SD) or median [range]. CAPS, cryopyrin-associated auto-inflammatory syndromes; HDx, haemodialysis; PD, peritoneal dialysis; SAH, subarachnoid haemorrhage.

**Table 2 T2:** Published PK and population PK parameter values for anakinra.

Reference	Population	N	Dose	Route	CL (l/h/70kg)	BSV CL (%)	V_D_ (l/70kg)
Yang B et al. (40)	Adults	341	30-150 mg	SC	6.92		9.94
Yang B et al. (30)	HD PD Normal GFR	10 10 12	1 mg/kg	IV	1.09 1.15 7.3		9.99 (initial 2.95) 9.8 (initial 3.26) 8.86 (initial 3.32)
Yang B 2003 (30)	Stratified by GFR	30	100 mg	SC	10.2 to 2.6		
Gueorguieva et al. (41)	Adult				6.96	23	5.14
Urien et al. (28)	Children	87	2-10 mg/kg	SC	6.24	54	6.52
Yang B et al. (38)	Adults Adults	32 32	100 mg 100 mg	IV SC	6.72 8.04		8.18

BSV, between-subject variability; CL, clearance; GFR, glomerular filtration rate; V_D_, volume of distribution.

There were 3 key considerations for extrapolation and simulation: size scaling of PK parameters, maturation of clearance mechanisms, and use of IV- versus SC-dosing. Modelling and simulation were performed, including between-patient variability, using the Berkeley Madonna software package (42). Graphs were rendered in R version 4.1.0 (43).

#### a) Size scaling

Size scaling of key pharmacokinetic parameters clearance (CL) and distribution volume (V_D_) was by theory-based allometry, with exponents ¾ and 1 for CL and V_D_, respectively. These are represented by equations 1 and 2:

CLi=CLSTD,70kg×(WTi70)34

VD,i=VD,STD,70kg×(WTi70)

Like many therapeutic drugs, anakinra is dosed in mg/kg in children. However, although this dosing strategy is safe and easy to implement, clearance mechanisms do not scale linearly with body weight. Provided clearance mechanisms are mature, per kilogram dosing leads to lower exposure in young (smaller) children, particularly below 2 years of age where systematic underexposure is seen (44). Two analyses of anakinra in children have confirmed lower exposure in younger children when given the same per-kilogram dose as older children and adolescents (28, 45).

Unlike per-kilogram dosing, scaling functions based on theory-based allometry, on the other hand, have both theory-based biological underpinning and extensive observational support (46). Their use is standard in drug development for small molecule drugs, for scaling across species to predict first-in-human dosing, as well as dose selection for paediatric clinical trials (47). More recently, these approaches have been shown to be predictive for therapeutic proteins as well, including down to neonatal size (32).

In a population PK analysis of anakinra in 87 children and adolescents, the authors defined an alternative scaling function for clearance (28). However, deviations from allometric scaling can relate to sampling distribution from insufficient sample size, and whilst the authors suggested that for therapeutic proteins the allometric model may not apply, subsequent literature for a range of therapeutic proteins has provided support for allometric scaling, including anakinra (32). Further, use of the scaling function in (28) would lead to substantially higher per-kilogram dosing in premature neonates (~10 mg/kg versus 3 mg/kg). We thus favoured use of the allometry, as it is both well supported and safer in our target population.

The impact of size scale used on per-kilogram dosing can be seen in **Figure 1**, noting that in premature neonates in the 500 g to 2 kg weight range, there is substantial under-dosing with per-kilogram dose, along with much higher dose from (28), compared to theory-based allometry.

**Figure 1 f1:**
[figure not shown]
Comparison of calculated dose (mg/kg) for linear, theory-based allometry and data-driven methods (28).

#### b) Maturation

After birth, renal function typically is sluggish in extremely premature neonates, with median inulin clearance expected to be <2.5 ml/min for the first 3 weeks after birth (duration of dosing) (48). Scaled for size, this is below the threshold of 30 ml/min/1.73 m^2^ (49–51), with overall clearance of anakinra thus expected to be reduced by 75% and alternate daily dosing being recommended. For prediction of renal function, a maturation model was used (52), which estimates GFR as a fraction of adult size-scaled equivalent based on post-menstrual age and size. The model was developed from a pooled population analysis of GFR (n=923) using ideal markers of GFR (polyfructose, 51Cr-EDTA, mannitol or iohexol) (52).

Non-renal clearance mechanisms of anakinra have not been described, and caution is required in new drug use in premature neonates due in part to immaturity of various hepatic drug-metabolising enzymes (53). However, no such immaturities have been described for proteolysis of therapeutic proteins (54), and indeed increased endogenous proteolysis has been described in some instances (55). Further, noting the near-identical structure to endogenous IL-1Ra, it would presumably share the same proteolytic pathways, for which there is no evidence of immaturity in the newborn period [plasma abundance of endogenous IL-1Ra in term infants was 42 ± 69 pg/ml on day 1, falling to 27 ± 77 pg/ml on day 2-3 (56)]. Nevertheless, given limited data on therapeutic proteins in extremely premature infants and thus on a precautionary basis, simulations were performed both with assumption of mature and immature non-renal clearance to better understand the impact on exposure if indeed the specific proteolytic mechanism were to be immature.

#### c) IV versus SC

SC-dosing of anakinra was not considered appropriate for the trial, given reduced subcutaneous tissue stores and skin fragility in premature neonates. Therefore, in preterm infants, IV is the preferred route of administration.

IV administration translates to substantially higher peak concentrations (38, 57). Reassuringly, there have been trials in various cohorts of very-high-dose IV anakinra therapy (e.g. 5 mg/kg and more) without any new or greater rate of toxicities seen (27, 57); it can therefore be used IV without compromising the favourable safety profile [reviewed in (58)].

A second impact of IV dosing is shorter duration of exposure, with loss of the elimination-rate limiting slow absorption from a subcutaneous depot. When administered IV to individuals with normal renal function anakinra is rapidly cleared, hence use of multiple daily dosing in trials of IV anakinra in adults (57).

As discussed above, dosing recommendation for anakinra in the setting of severe renal impairment (as seen in our population) is for the same dose size administered alternate daily. However, to mitigate the above issues with IV administration – higher peak concentration and shorter duration of exposure – we considered administration of 50% of the dose daily. This is demonstrated schematically in **Figure 2**. With simulation of alternate daily dosing of 3 mg/kg IV, 1.5 mg/kg daily IV, and for comparison 1.5 mg/kg SC daily, in an infant born at 25 weeks GA and 850 g birth weight.

**Figure 2 f2:**
[figure not shown]
Concentration-time course following IV administration alternate daily (dashed line), or daily at 50% dose, both IV (solid line with high peaks and SC (solid line with lower, rounded peaks).

#### d) Simulations

Initial dose recommendation based on product label is for 1 mg/kg daily, though in the setting of GFR<30 ml/min/1.73 m^2^, the same dose would be administered alternate daily. At the same time, allometric scaling would suggest a per-kilogram dose of 3 mg/kg daily in a neonate weighing 500g to 1 kg to give equivalent exposure to 1 mg/kg in a 70 kg adolescent. In the setting of GFR<30 ml/min/1.73 m^2^, this would equate to 3 mg/kg alternate daily or, based on above considerations for IV dosing,1.5 mg/kg daily.

Various dosing regimens were simulated, using population PK parameters of anakinra, population parameter variability, and scaling for size and maturation of renal function. In addition, simulations were performed with 50% and 75% reduction in non-renal clearance, to assess impact on exposure. For each dosing regimen and population, 1000 simulations were performed and compared to literature values. Based on simulations and literature comparisons, notably including a threshold of 9.6 mg/l x h identified as the exposure above which sufficient suppression in auto-immune disease is achieved (28), a dose of 1.5 mg/kg daily was deemed the optimal dosing regimen.

However, if this predicted optimal dosing rate of 1.5 mg/kg daily were used from the start and non-renal clearance were immature, this dosing rate would lead to excessive exposure, beyond that seen in older children receiving 3 mg/kg daily of anakinra. This eventuality is avoided with the planned staged approach, in which the first 6 participants receive 1 mg/kg alternate daily, followed by interim PK analysis. The rationale for this decision is as follows. Keeping the threshold of 9.6 mg/l x h in mind beyond which sufficient anti-inflammatory activity can be expected (28), **Figure 3** depicts simulations in studied populations (A-E) and extrapolated populations (F-I), with F and G depicting the predicted exposure if non-renal clearance is fully mature, H and I if non-renal clearance is only 25% mature. Assuming mature non-renal clearance, the stage 1 dosing regimen of 1 mg/kg alternate daily predicts exposure equivalent to 1 mg/kg in a child weighing 12 kg, whilst Stage 2 (optimal) dosing of 1.5 mg/kg daily predicts exposure equivalent to 3 mg/kg in a child of 12 kg. Interim analysis after the first six participants will allow confirmation of non-renal clearance being mature, and enable safe progression to the 1.5 mg/kg daily dosing schedule. On the other hand, in the unlikely case that non-renal clearance is immature (for example at 25% maturity), the initial dosing regimen of 1 mg/kg alternate daily will lead to exposure close to that seen with dosing rate of 3 mg/kg daily in an older child. If non-renal clearance were found to be immature at interim analysis, dosing in Stage 2 would be adjusted accordingly.

**Figure 3 f3:**
[figure not shown]
IL-1Ra plasma exposure (AUC_0-24_) from 1000 simulations, in studied populations and extrapolated to extremely premature neonates. Simulated exposure for **(A)** a 70 kg adult receiving 100 mg daily, **(B)** a 70 kg adult with severe renal impairment receiving 100 mg daily, **(C)** a 70 kg adolescent receiving 1 mg/kg daily, **(D)** a 2-year-old child weighing 12 kg and receiving 1 mg/kg daily, **(E)** a 12 kg 2-year-old child receiving 3 mg/kg daily. Simulations in extrapolated PK: **(F)** an extremely premature neonate (25-weeks GA, 850 g) with mature non-renal clearance receiving 1 mg/kg alternate daily, **(G)** an extremely premature neonate receiving 1.5 mg/kg daily, **(H)** an extremely premature neonate with 25% function of non-renal clearance receiving 1 mg/kg alternate daily, and **(I)** an extremely premature neonate with 25% function of non-renal clearance receiving 1.5 mg/kg daily. The dashed line indicates the threshold of 9.6 mg/l x h identified in (28) as the exposure above which sufficient suppression in auto-immune disease is achieved.

The concentration-times for the 4 scenarios are shown in **Figure 4**. i.e. Stage 1 and 2 dosing with mature (**Figures 4A, B**), then immature non-renal clearance (**Figures 4C, D**). Maximum concentrations are consistent with published experience, and accumulation only occurs in a limited fashion in the Stage 2 regimen with immature non-renal clearance, not in any other scenario.

**Figure 4 f4:**
[figure not shown]
Concentration-time course for 1000 simulations (2.5^th^/25^th^/50^th^/75^th^/97.5^th^ centiles, indicated by solid, dashed, red, dashed and solid lines in this order, respectively), for different scenarios of anakinra IV dosing in an extremely premature neonate. **(A)** 1 mg/kg alternate daily, mature non-renal clearance; **(B)** 1.5 mg/kg daily, mature non-renal clearance; **(C)** 1 mg/kg alternate daily, non-renal clearance at 25% maturity; **(D)** 1.5 mg/kg daily, non-renal clearance at 25% maturity.

### Summary dosing strategy

For Stage 1, six infants will receive 1.0 mg/kg IV given alternate daily from day 1 to day 21 after birth. In the event of acute kidney injury (AKI), detection during blood monitoring within the 3 weeks of treatment, anakinra treatment will be halted until renal function has recovered as defined below.

After completion of Stage 1, the Investigators and the data safety monitoring board (DSMB) will conduct an interim analysis, including assessment of mortality and rate of complications of prematurity, and comparison of observed exposure with the predicted exposure estimated from the population PK simulation. If appropriate, with confirmation of mature non-renal clearance within the first cohort of 6 infants, Stage 2 will administer 1.5 mg/kg per day for the remaining 18 infants. Furthermore, dosing will not need to be withheld in the setting of acute kidney injury (AKI) if non-renal clearance is confirmed to be mature from birth.

### Resulting overall protocol algorithm

A flow chart illustrating the protocol resulting from the considerations discussed above is shown in **Figure 5**.

**Figure 5 f5:**
[figure not shown]
Anakinra Pilot flow chart. DSMB, Data Safety Monitoring Board; USS, ultrasound study; MRI, magnetic resonance imaging; PK/PD, pharmacokinetic/pharmacodynamic analysis; FBE, full blood examination; UEC, urea, electrolytes, creatinine. *, Publication will not await these result, 2 year follow-up results will be published separately.

### Indications for interruptions of treatment

Treatment will continue until day 21 unless one of the following occurs: a suspected unexpected serious adverse reaction (SUSAR); acute kidney injury, which will increase dose-normalised exposure if immature nonrenal clearance is demonstrated in Stage 1; neutropenia; or elevation of liver enzymes. To monitor for these events, the following blood tests will be sent to hospital pathology on days 3, 7 and 14 after birth: FBC, ALP, ALT, UEC.

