#### Serious infection

Anakinra at higher doses (>100 mg SC daily in adults) has been associated with an increased risk of development of infection (25). However, whether or not it is sensible to withhold anakinra in an individual who develops an infective episode is unclear. Anakinra has been used in large randomised controlled trials of sepsis (>1000 patients) as well as syndromes associated with cytokine storm, showing some evidence of benefit and no signal of increased morbidity/mortality (62). In the sepsis trials, anakinra was given over the initial 72 h (57), thus safety in the setting of infection beyond 72 h cannot be assumed. In the event of a positive blood culture and clinical signs of sepsis, anakinra will be withheld if the neutrophil count is <0.5 x 10^9^/l and/or circulatory support with infusion of inotropic medications is required and cannot be weaned 48 h after commencement. Anakinra can be recommenced with recovery of the neutrophil count to >0.75 x 10^9^/l or cessation of inotropic treatment.

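### The safety-lab schedule is stated in two incompatible ways, and the sepsis hold and restart rules can both apply to the same infant

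*Protocol article*

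**What the plan says.** Three parts of the protocol article govern interruption of anakinra.

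- **Estimated duration of individual subject participation.** Treatment runs to day 21 unless a SUSAR, acute kidney injury, neutropenia or raised liver enzymes occurs. To watch for these, "the following blood tests will be sent to the routine pathology laboratory on days 1, 3, 7, 14, and 22 after starting IL-1Ra infusions". The last two events appear as "neutropenia; or elevation of liver enzymes (details below"), which points the reader to later text. On timing: "Anakinra treatment commences at 3-24 hours of postnatal life and ceases on postnatal day 21".
- **Indications for interruptions of treatment.** The same four events are listed and the same monitoring purpose is given, but here "the following blood tests will be sent to hospital pathology on days 3, 7 and 14 after birth: FBC, ALP, ALT, UEC".
- **Serious infection.** Given a positive culture together with clinical sepsis, "anakinra will be withheld if the neutrophil count is <0.5 x 10^9^/l and/or circulatory support with infusion of inotropic medications is required" and has not been weaned by 48 h. Then: "Anakinra can be recommenced with recovery of the neutrophil count to >0.75 x 10^9^/l or cessation of inotropic treatment".

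The Safety and Feasibility definitions both refer to finishing the treatment. Safety also requires no excess of adverse events.

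**The concern.** A reader who follows one section draws blood on different days, counted from a different starting point, than a reader who follows the other. Both sections claim to monitor for the same events.

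In the Serious infection section, the hold is joined by and/or while the restart is joined by or. Read literally, recovery of one trigger permits dosing while the other still requires withholding.

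The general lists also name neutropenia by itself, although the only neutrophil threshold in the article sits inside the sepsis rule.

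At stake are patient safety, uniform exposure within a dosing stage, and consistent counting of completed courses. In Stage 1 each infant is 1/6 of the cohort whose complications and exposure inform the decision on Stage 2 dosing.

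**Working it through.** The plan gives no figure to reproduce here. The check sets the passages side by side.

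**1. Lab days**

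| | Estimated duration section | Indications for interruptions section |
|---|---|---|
| Days | 1, 3, 7, 14, 22 | 3, 7, 14 |
| Counted from | start of infusions | birth |
| Panels per infant | 5 | 3 |
| Panels up to day 21 | 4 | 3 |

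- Days found only in the first list: 1 and 22. Days found only in the second: none.
- Clock offset: treatment starts at 3 to 24 h of life, so 3/24 = 0.125 day to 24/24 = 1 day.
- Panels over 24 infants: 5 × 24 = 120 against 3 × 24 = 72. The 48 extra panels are 24 on day 1 and 24 on day 22.
- Dosing stops on day 21, so the day-22 panels cannot trigger a hold. The on-treatment difference is 4 × 24 − 3 × 24 = 24 panels, one per infant, plus the clock offset.
- After day 14, 21 − 14 = 7 treatment days remain (7/21 = 33%, by nominal day number). Neither schedule has a panel in that week. They differ only in that the first has a later panel, on day 22, which would pick up abnormalities still present then.

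**2. Hold and restart in sepsis**

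Take an infant with culture-positive sepsis who is held for both reasons. Illustrative neutrophil counts are 0.4 and 0.8 × 10^9/l. Clinical sepsis is assumed to persist, and each clause is read literally.

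| State | Hold clause met? | Restart clause met? |
|---|---|---|
| 0.4, inotropes still running after 48 h | yes | no |
| 0.4, inotropes stopped | yes (count <0.5) | yes (inotropes ceased) |
| 0.8, inotropes still running | yes (inotropes) | yes (count >0.75) |
| 0.8, inotropes stopped | no | yes |

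The two middle rows satisfy both clauses. An infant held for one reason only does not produce the clash, because the other trigger was never present and so has nothing to recover from.

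**3. Interruption lists against the detailed rule**

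- Neutrophils 0.4 without sepsis: neutropenia is on both general lists, with no threshold. The sepsis rule does not apply.
- Sepsis, neutrophils 0.8, inotropes not weaned at 48 h: held under Serious infection, but neither general list names inotropes.

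**4. Weight of one infant**

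- Whole trial: 1/24 = 4.2 percentage points. Stage 1: 1/6 = 16.7 percentage points.
- For orientation, the quoted baseline rate of late-onset sepsis is 27%, and 0.27 × 24 = 6.5 infants. Only some of these would have positive cultures within 21 days and both triggers. The article gives no figure for that fraction.

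**The case against.** **Lab schedule.** The shorter list may be an abbreviation: it does not say only these days, and all its day numbers appear in the longer list. The Blood sampling procedure section takes samples on days 1, 3, 7, 14 and 22, which suggests the longer list is the fuller one. The flow chart may show the schedule but is not available here. In addition, blood results obtained for clinical reasons are recorded under Safety monitoring, and ALT above three times the upper limit must be repeated within 48 h. These points soften the consequence. They do not explain why the text gives two clocks, and nothing in it says which list governs.

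**Restart.** Each recovery criterion could be meant to pair with its own trigger. Alternatively, the hold (will be withheld) could be mandatory and override a permissive restart (can be recommenced). Either reading removes the clash, but the text states neither.

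**Neutropenia.** The general lists may be mere headings, and a condensed article may leave a threshold for isolated neutropenia to the full protocol. This largely stands, which is why the point is secondary.

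**Stronger readings that the documents do not support.**

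- A reader might infer that the sections contradict each other on whether neutropenia alone stops treatment. Serious infection never says that isolated neutropenia is treated through.
- A reader might infer that laboratory results drive every hold. SUSARs, anuria and inotrope need do not depend on these panels.
- A reader might infer that the shorter schedule loses a baseline test. Day 1 after starting infusions is not clearly a pre-dose sample.
- A reader might blame the mismatch for the week without on-treatment tests. That gap exists under both schedules.

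**Conclusion.** The concern holds in limited form.

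- **Lab schedule:** a direct inconsistency in days and anchor for one stated purpose. Its on-treatment size is one panel per infant and an offset of 3 to 24 h. The day-22 panel bears on safety capture after day 14, not on dosing.
- **Sepsis rule:** a logical overlap within a single section, confined to septic infants held for both reasons. It rests on a literal reading of the two conjunctions and on sepsis persisting when the rule is reapplied.
- **Interruption lists:** a lesser lack of alignment, not two opposing statements.

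No sample size or analysis figure changes. The number of infants whose course would be classified differently cannot be derived from the article. The point still deserves correction, because these rules affect participants directly and treatment completion enters both primary definitions.

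**What to change.** - State one lab schedule with one time anchor, identically in Estimated duration of individual subject participation and Indications for interruptions of treatment.
- Reword Serious infection so that no infant can satisfy the hold and restart criteria together.
- Align the two general interruption lists with Serious infection, for both neutropenia and the inotrope hold.

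Which days, thresholds and restart conditions apply is for the investigators and the DSMB to decide; this review takes no position on the clinical content. The cost is protocol wording. The article already describes these blood tests as part of standard care.
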